#### Secondary Outcomes - Neurophysiological

For Aim 3, variables will be analyzed with a mixed model, with fixed effects of TEST TIME (Baseline, Post, 1, 4, 6 M), sensorimotor cortex (Ipsilesional, Contralesional), Muscle (Intrinsic, Extrinsic) and Treatment Group (EVR, DVR, DMUC, UC). AREA (size of the cortical surface area in the affected hemisphere where MEPs can be elicited, to be used as an index of focusing of the cortical excitability distribution) will be used as an outcome measure. In addition to group analyses, we will use a Spearman rank order test to correlate individual subject measures of cortical topography (Area/Volume/COG shift, measured by TMS mapping) and clinical measurements of impairment (hand/wrist UEFMA) and function (distal WMFT) across testing time points. In our experience, individual subject data analysis has proven invaluable in understanding the effects of therapy on functional recovery. Non-parametric statistics (Kruskal-Wallis or Mann-Whitney) will be used for variables that fail tests of normality. Alpha level will be set at 0.05. Tukey *post-hoc* tests will be used to investigate significant interactions.

Lesion size and location (cortical/subcortical) will be used for secondary analyses regarding responders/non–responders, etc. (56–58) in which we used theory-based categorization of brain lesions to determine regions associated with better response to stroke rehabilitation, using a mixed-model analysis.

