#### Secondary Outcomes-Neurophysiological

The neurophysiological outcomes include cortical area representation of the finger-hand muscles as measured by Transcranial Magnetic Stimulation (TMS), and brain connectivity as measured through Electroencephalography (EEG). TMS mapping and EEG data will be acquired at pre- and post-therapy and at 4 months post stroke (see Table 2).

**Table 2 T2:** Assessment schedule for the outcome measures.

**Measure**	**Domain measured**	**Pre-test^**^**	**Post-test**	**1 month**	**4 months**	**6 months**

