**Secondary outcomes – neurophysiological**						
TMS - MEP amplitude and extent	Patterns of cortical reorganization	x	x		x	
EEG	Resting state/task-based brain connectivity	x	x	x	x	x

* *ideally within 72 h after Post-test*.

** *The delayed VR group has two PRE tests, one in the hospital and one immediately prior to the delayed VR intervention*.

*Patterns of Corticospinal Reorganization* will be assayed using single-pulse TMS (Magstim Rapid with an AirFilm Coil). Changes in the ipsilesional and contralesional hand cortical territory will be quantified using motor evoked potentials (MEPs) in persons that meet specific safety criteria for TMS. The topographic representation of the following hand and arm muscles will be mapped before and after training and at the three retention time points: first dorsal interosseous [FDI], extensor indicis longus [EI], abductor pollicis brevis [APB], abductor minimi [ADM], flexor digitorum superficialis [FDS], extensor digitorum communis [EDC], flexor carpi radialis (FCR), extensor carpi radialis [ECR], extensor pollicis longus [EPL], and brachioradialis [BR]. To ensure spatial precision we will employ frameless neuronavigation (Brainsight, Rogue Research, Inc.).

A threshold of 50 uV will be used to detect MEPs against background EMG (45). MEP amplitude will be measured as the peak-to-peak amplitude of the EMG signal 20–50 ms after the TMS pulse. In addition, the amplitude of the background EMG will be calculated as the area under the EMG envelope in the 50 ms interval before the TMS pulse where the envelope is generated by filtering the signal with 2nd order Butterworth filter (5–250 Hz band-pass), full-wave rectifying the filtered signal and applying 20 Hz low-pass filter. MEP and background EMG amplitude will be estimated for each muscle and for each stimulation point. MEP amplitudes and coordinates of the stimulation points will be interpolated to a 7 × 7 cm mesh of 5 mm resolution centered on the M1 hotspot using cubic surface interpolation method (46, 47). This will allow comparisons across maps and sessions. The weighted-average location of corticospinal output devoted to a muscle, or center of gravity (COG), is expressed as an MEP-weighted centroid of the cortical representation in the rostral-caudal (COGx) and medial-lateral (COGy) plane using standard equations (45, 48).

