### Statistical Analysis

The primary aim of the study is to test, at 4 months post-stroke, whether intensive VR/Robotic motor training initiated 5–30 days post-stroke, improves functional outcomes of the hemiparetic arm and hand when compared to VR/Robotic motor training initiated on 30–60 days post-stroke. Other comparsions include evaluating the type of training (EVR vs. DMUC) and dosing (DMUC vs. UC) initiated within 5–30 days post-stroke. The secondary aims will systematically investigate the mechanisms underlying the changes resulting from the early timing of training and increased dosing. Aim 2 will quantify the recovery and compensation profiles by examining the changes in kinematics and kinetics of the hand and arm associated with this training and Aim 3 will quantify patterns of cortical somatotopic reorganization and will investigate the relationship among these patterns of reorganization and the clinical and biomechanical outcomes.

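### The Aim 3 link between cortical maps and clinical scores is tested by an ordinary Spearman correlation across visits, with no unit of analysis and no handling of repeated measures

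*Protocol article*

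**What the plan says.** All references are to the protocol article.

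- *Study Aims and Hypotheses* expects functional gains to go with expansion of the ipsilesional hand representation. *Statistical Analysis* makes this part of Aim 3, which "will investigate the relationship among these patterns of reorganization and the clinical and biomechanical outcomes".
- *Secondary Outcomes - Neurophysiological* (under Statistical Analysis) gives a mixed model for map area. In addition to that model, "we will use a Spearman rank order test to correlate individual subject measures of cortical topography" (area, volume and centre-of-gravity shift) with "clinical measurements of impairment (hand/wrist UEFMA) and function (distal WMFT) across testing time points". The reason offered is that "individual subject data analysis has proven invaluable in understanding the effects of therapy on functional recovery". The same paragraph adds "Alpha level will be set at 0.05". It does not say whether visits are pooled, taken one at a time, reduced to changes or analysed within each patient.
- The number of TMS visits differs between places. The neurophysiological section under Measures says "TMS mapping and EEG data will be acquired at pre- and post-therapy and at 4 months post stroke", and Table 2 marks the same three visits for TMS. The text below Table 2 says that the muscles will be "mapped before and after training and at the three retention time points", which makes five, and the Aim 3 model uses "TEST TIME (Baseline, Post, 1, 4, 6 M", also five. A footnote to Table 2 gives the delayed VR group a second pre-test.
- *Multivariate Regression Analyses* adds a regression of ARAT, Fugl-Meyer or Box and Blocks on neurophysiological scores, labelled hypothesis-generating.

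**The concern.** An ordinary Spearman test assumes independent pairs, but the sentence spans repeated visits on the same patients and names no adjustment. The mixed model in the same section handles repeated visits for map area as an outcome. It does not cover the correlation.

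Patients are followed from shortly after stroke to six months, so clinical scores and maps may both change with time for reasons unrelated to each other. Pooled visits mix three things: differences in severity between patients, the common course of recovery, and the within-patient association that the hypothesis is about. A positive pooled result could come from the first two alone. A within-patient test on three visits could not support the hypothesis in any patient. With the unit left open, the choice could be made after the data are seen.

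**Working it through.** The article gives no sample size, power or error rate for this correlation, so there is no figure of its own to reproduce. Each possible reading was checked in turn.

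**Inputs**
- Visits T: 3 (Measures text and Table 2) or 5 (text below Table 2 and Aim 3 model).
- Patients: 96 required, 120 planned (*Sample Size*). The number eligible for TMS is not given, so 30 was also tried.
- Within-patient correlation ρ: 0.7 is stated in *Sample Size*, for ARAT only. Its use for maps and clinical scores is an assumption, so the range 0.5–0.9 is shown.
- Alpha 0.05. Two-sided testing is assumed, because sidedness is not stated.

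**1. Visits pooled, no true association.** With compound symmetry in both measures, the variance of the correlation is inflated by about 1 + (T − 1)·ρ_x·ρ_y, and the actual level is 2·[1 − Φ(1.96/√inflation)]. At ρ = 0.7:
- T = 3: 1 + 2 × 0.49 = 1.98, level 0.164
- T = 5: 1 + 4 × 0.49 = 2.96, level 0.255

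Simulation of the ordinary Spearman test (96 patients, 4,000 runs per cell) agrees:

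| ρ in both measures | 3 visits: formula | 3 visits: simulated | 5 visits: formula | 5 visits: simulated |
|---|---|---|---|---|
| 0.5 | 0.110 | 0.105 | 0.166 | 0.157 |
| 0.7 | 0.164 | 0.160 | 0.255 | 0.248 |
| 0.9 | 0.226 | 0.210 | 0.341 | 0.342 |

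The number of patients hardly matters. At ρ = 0.7, 30 and 120 patients give 0.157 and 0.152 with three visits, and 0.247 and 0.248 with five.

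**2. Visits pooled, with a common recovery trend but no individual link.** The size of such a trend is not in the article, so these values are illustrative (96 patients, ρ = 0.7, 2,000 runs for each non-zero trend):

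| Linear trend over follow-up, both measures | 3 visits | 5 visits |
|---|---|---|
| none | 0.16 | 0.25 |
| 0.5 SD | 0.19 | 0.28 |
| 1 SD | 0.66 | 0.61 |

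**3. Within one patient.** Without ties, n visits have n! equally likely orderings under no association, so the smallest exact two-sided p is 2/n!:
- n = 3: 2/6 = 0.333
- n = 4: 2/24 = 0.083
- n = 5: 2/120 = 0.017, only at |rho| = 1; the next value, 0.9, gives 0.083
- n = 6: 2/720 = 0.003

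The values 4 and 6 would apply to the delayed VR group if TMS is done at both of its pre-tests. A one-sided test does not rescue three visits (1/6 = 0.167).

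**4. One pair per patient.** With one row per patient, the simulated level is 0.049–0.055 for 30, 96 and 120 patients. This holds for a single visit or for a change score. At a single visit, however, the correlation of levels reflects how severely each patient is affected. Only the change version matches a hypothesis about gains and expansion.

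**The case against.** The strongest reply is that the article never says visits will be pooled. It speaks of individual subject measures, and a centre-of-gravity shift is naturally a change between sessions. One pair per patient is therefore a possible reading, and it is valid. A condensed article may leave the unit of analysis to the full plan. The correlation is also an addition to a mixed model, and a hypothesis-generating regression addresses the same link.

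Much of this stands, and it rules out several stronger conclusions that a reader might draw:
- *That the plan commits to a pseudo-replicated test.* It does not. The error rates above apply only if visits are pooled.
- *That a within-patient test can never be significant.* This is true for three visits. It is not true for five, nor for six in the delayed VR group. The statement depends on a visit schedule that the article contradicts.
- *That the false-positive rate is about 60%.* That rests on a 1 SD trend which appears nowhere in the article; at 0.5 SD the rate is 19–28%.
- *That the link would otherwise go unexamined.* The regression also covers it, as exploration. The within-person correlation which that section mentions modelling is that of VR measurements.

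The reply does not dispose of the point. The article names the test, its span over visits and its alpha, so more is fixed than a detail left for later. Area and volume are not changes by nature, and nothing selects the change-score reading, which is the only one of those checked that both keeps its level and answers the stated hypothesis.

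**Conclusion.** The point holds as a defect in a secondary, mechanistic analysis. As worded, the Spearman test admits readings of very different worth:
- Pooled over visits, its type I error is about 10–21% (three visits) or 16–34% (five), assuming a within-patient correlation of 0.5–0.9 in both measures and no trend. A common recovery trend adds to this by an amount that the article does not allow one to fix.
- Within a patient, it cannot reach 0.05 on the three-visit schedule, and on five visits it does so only at a perfect ordering.
- Across patients at one visit, it is valid but tests a different question.

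The primary ARAT comparison, the sample size and the treatment contrasts are not touched.

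**What to change.** 1. Define the Aim 3 association as a Spearman correlation with one pair per patient: Pre-to-4-month change in map area against Pre-to-4-month change in one named clinical score. TMS is planned at both times under either version of the schedule. State which of the two pre-tests serves as Pre in the delayed VR group.
2. Choose a clinical score that is scheduled, for example the hand/wrist part of the Fugl-Meyer. The WMFT named in the present sentence is neither among the listed outcomes nor in Table 2.
3. If all visits are to be used, replace Spearman with a repeated-measures correlation, or with a mixed model of the clinical score on patient-centred map area, with Test Time and Treatment Group as fixed effects and patient as random effect.
4. Reconcile the TMS visits: three in the Measures text and Table 2, five in the text below Table 2 and in the Aim 3 model.

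The cost is revised analysis wording and a few lines of code. No new data are needed if the score is one already scheduled.

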We will use the robust mixed effect model approach to analyze the data. We demonstrated in the past that this analytic approach is robust to detect treatment effects, even with relatively small groups of patients in whom within-group variance occurs with respect to stroke characteristics (56). Test Time (Pre, Post, 1-month post-treatment, 4 months post-stroke, 6 months post-stroke) and Treatment Group (EVR, DVR, DMUC, UC) will be treated as fixed effects in the mixed models. The interaction term between Test Time and Treatment Group will be included. Baseline measurements will be added as a covariate into mixed models for outcome variables. Random intercept will be used to model subject-level variation. Covariance pattern and model selection will be implemented with likelihood-based tests. Contrasts to compare group means will be applied to obtain comparisons between time, and between treatments, with multiplicity adjustment considered. We have an a priori interest in specific Test Time by Treatment Group interaction effects for the EVR-DVR, for the DMUC-UC, and for the EVR-DMUC comparisons. The particular differences we are interested in are Pre vs. Post and Pre vs. second (4 months post stroke) retention assessments. In the case of balanced data and equal variances, we will use the Tukey procedure to test for significant interaction effects, otherwise, Bonferroni correction will be used. In our design, the timing comparison is the difference between EVR and DVR. The dosage comparison is the difference between UC (usual care) and the DMUC (usual care plus 10 additional hours). In addition, we will be able to compare the type of training effect, VR vs. dose-matched usual care (EVR vs. DMUC), where both types of training are delivered in the same time period.

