#### Management of Statistical Assumptions

For all analyses, model-related assumptions will be examined. For example, in case that normality assumption required by linear mixed effects model cannot be met, appropriate transformation to center the dependent variables will be first sought. If no appropriate transformation is applicable, non-parametric mixed models will be applied. Collinearity between covariates will be examined with variance inflation factor (multilevel variance inflation factor to the case of mixed effects models). Appropriate selection from collinear covariates will be based on knowledge or literature. Statistical methods like principal component analysis will be used to extract factors from collinear covariates when needed.

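### Aim 3 variables that fail a normality test are sent to Kruskal-Wallis or Mann-Whitney, which conflicts with the plan's general rule and does not fit the repeated-measures design

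*Protocol article*

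**What the plan says.** Under Secondary Outcomes - Neurophysiological, the protocol article sets out the Aim 3 analysis as follows: "For Aim 3, variables will be analyzed with a mixed model, with fixed effects of TEST TIME (Baseline, Post, 1, 4, 6 M", with further fixed effects for cortex (two levels), muscle group (two) and treatment group (four). Tukey post-hoc "tests will be used to investigate significant interactions", and "Alpha level will be set at 0.05".

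The same paragraph gives the fallback: "Non-parametric statistics (Kruskal-Wallis or Mann-Whitney) will be used for variables that fail tests of normality".

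Two other sections bear on it:

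- Statistical Analysis, on the general model: "The interaction term between Test Time and Treatment Group will be included" and "Random intercept will be used to model subject-level variation".
- Management of Statistical Assumptions opens with "For all analyses, model-related assumptions will be examined". For a failure of the normality assumption in a linear mixed model it asks first for a transformation, and then: "If no appropriate transformation is applicable, non-parametric mixed models will be applied".

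**The concern.** One event, a non-normal Aim 3 variable, leads to two different prescribed analyses. One keeps the longitudinal structure. The other drops it, skips the transformation step, and is triggered by a test on the variable, although the mixed model's assumption concerns residuals and random effects. With both on the page, the choice can be made after the results are seen.

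The rank tests also do not match the design. Each patient contributes values at several visits and, by the model's own factors, for more than one cortex and muscle group. Kruskal-Wallis and Mann-Whitney have no patient effect and no interaction term. Run on all rows, they count repeats as separate patients. Run on one visit, they compare levels at that visit and not change between arms. At stake is the validity or the relevance of the p-values behind Aim 3's claims about mechanism.

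**Working it through.** The plan states no figure that depends on this sentence, so there is none to reproduce. The check is a comparison of the text and an illustration of size.

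**1. The rules side by side**

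| | Neurophysiological section | Management of Statistical Assumptions |
|---|---|---|
| Scope | Aim 3 variables | all analyses |
| Trigger | variable fails a normality test | normality required by the mixed model is not met |
| First step | rank test | transformation |
| Second step | none | non-parametric mixed model |
| Within-patient dependence | not handled | handled |
| Interaction | not available in the named tests | available |

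Neither section refers to the other or states an exception.

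**2. Inputs for the illustration**

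- Arms: 4, with 24 patients each (Sample Size).
- Nominal level: 0.05 (Aim 3 text).
- Rows per patient: 3, from the TMS schedule in Table 2 (pre, post, 4 months), or 5, from the Aim 3 model's time levels.
- Within-patient correlation ρ: assumed, 0.3 to 0.7. Sample Size gives 0.7 for the ARAT calculation. The document gives none for TMS measures.

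**3. Kruskal-Wallis on pooled rows, no true group difference**

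With T equally correlated rows per patient, the statistic is inflated by about D = 1 + (T − 1)ρs, where ρs = (6/π)·arcsin(ρ/2) is the rank correlation. The actual error is about P(χ²₃ > 7.815/D).

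| T | ρ | ρs | D | 7.815/D | Approximate error | Simulated (two sets, 2,000 runs each) |
|---|---|---|---|---|---|---|
| 3 | 0.3 | 0.288 | 1.575 | 4.96 | 17.5% | 16%, 17% |
| 3 | 0.5 | 0.483 | 1.965 | 3.98 | 26.4% | 26%, 26% |
| 3 | 0.7 | 0.683 | 2.366 | 3.30 | 34.7% | 35%, 35% |
| 5 | 0.3 | 0.288 | 2.150 | 3.63 | 30.4% | 28%, 30% |
| 5 | 0.5 | 0.483 | 2.930 | 2.67 | 44.6% | 45%, 46% |
| 5 | 0.7 | 0.683 | 3.732 | 2.09 | 55.3% | 54%, 57% |

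With one row per patient the simulated error stays near 5%.

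**4. Mann-Whitney with one value per patient**

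Two arms of 24, two visits, ρ = 0.7, and a pure crossing interaction with a difference in differences of 0.8 SD (assumed). Rejection rates over 4,000 simulated trials were:

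- mean of the two visits: 5%, so no power for the interaction;
- second visit alone: 27%, reflecting only the difference in level at that visit;
- change score: 92%.

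A rank test can therefore address a two-visit Time by Group contrast, but only on a per-patient change score, which the Aim 3 text does not name.

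**The case against.** The strongest reply is that the text never says the rank tests would be run on pooled rows. How they would be applied is detail that an article may leave to a fuller plan. A rank test on one pre-to-4-month change per patient is valid, and Statistical Analysis already names Pre vs. Post and Pre vs. 4 months as the differences of interest. The fallback sentence also follows text on Spearman correlations and individual-subject data, so it may be meant for simple comparisons, with the general rule still governing the mixed model.

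Much of this stands, and it rules out several stronger readings that a reader might infer:

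- **That these tests can never address Time by Group.** They can, on a change score.
- **That Aim 3 will have a grossly inflated error rate.** The pooled-row figures are conditional on an analysis the document does not specify. Counting hemispheres and muscle groups as further rows would raise them, but AREA is defined for the affected hemisphere only, and no correlation across those cells is given.
- **That about half the information is lost by ignoring baseline.** This would need the 0.7 from the ARAT calculation to hold for TMS maps, and a single-visit analysis.
- **That the fallback is bound to be triggered because two of the four strata are MEP-negative.** Strata are not patient counts. Patients ineligible for TMS are placed in strata without being mapped, and the article expects moderate patients to have MEPs. The share of zero areas cannot be derived.

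What does not fall is the conflict. The general rule claims all analyses, the Aim 3 sentence covers variables assigned to a mixed model in the same paragraph, and it is not limited to simple comparisons. This is a contradiction in the text shown and not an omitted detail.

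**Conclusion.** The concern holds as a conflict between two stated rules, together with a fallback that does not fit the design as written. It should be corrected, but it does not threaten the trial's main result: only secondary Aim 3 outcomes are affected, and the ARAT analysis and the sample size are untouched.

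The size depends on use. On pooled rows, type I error would be roughly 16–35% with 3 visits and 28–57% with 5, at assumed correlations of 0.3 to 0.7. On one visit or on patient means, the level would be held but Time by Group would go untested. On one change score per patient, the test would be sound for that single contrast. The figures rest on equal correlation between visits, 24 patients per arm and no true group difference. They show why the sentence matters and do not predict what will happen.

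**What to change.** Replace the fallback sentence in the neurophysiological section with a reference to Management of Statistical Assumptions: assess the residuals of the Aim 3 mixed model, seek a transformation if they are unsatisfactory, and otherwise use a non-parametric mixed model. Add that Kruskal-Wallis and Mann-Whitney apply only to variables with one value per patient, such as a named Pre-to-Post or Pre-to-4-month change score.

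The cost is one sentence and slightly more programming. No sample size, visit or measurement changes.
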